#### 2.4.2. Shear Wave Elastography (SWE) Assessment

The SWE elastography will collect complementary additional and improved data. In fact, the muscles analyzed are fundamental for trunk stability. Their stiffness and the consequent intra-abdominal tension are important in health and motion [12,33,34]. Shear-wave elastography (SWE) data collection uses the muscle shear module using an Acuson Sequoia Ultrasound System 2018 (Siemens Healthcare GmbH, Erlangen, Germany). This device is coupled with a linear transducer array (SL10-4, 4–10 MHz, Siemens Healthcare GmbH, Erlangen, Germany) in the shear-wave elastography mode, namely the musculoskeletal pre-set and B-mode [35].

The shear-wave elastography system uses the mechanical properties of muscle hardness and represents the transverse’s muscle stiffness. In technical terms, shear waves are generated within the muscle under evaluation, propagating through it. These waves are then quantified by measuring the shear wave velocity (Vs) using a specific algorithm, all in a non-invasive manner (see Figure 1). A higher shear wave velocity indicates greater muscle elasticity. This method is applicable even for assessing muscles at deeper layers. The shear modulus (μ) is calculated using the shear wave velocity (Vs) as follows: μ = ρ × Vs^2^, where ρ represents the muscle mass density (1000 kg/m^3^) [36]. The push frequency is automatically configured by the ultrasound equipment to approximately 1 Hz, falling within the range of 0.8 to 1.4 Hz [13,37].

The procedure will be carried out by the same experienced ultrasound operator, to avoid interobserver variation. The ultrasound device, transducer, setup parameters, and assessment locations will be identical for all assessments. The transducer location for the TrA muscle was established previously. The determination of the transducer location for all muscles is based on methodologies employed in prior SWE studies (refer to Table 3). The examiner will use a waterproof ink pen to mark the target region directly on the subject’s skin. This target region is situated on the right side of the umbilicus and extends 2 cm inward from the mid-axillary line. The linear transducer array is positioned on the target region in a transverse orientation to the body’s long axis, aligning it parallel to the muscle fibers of the TrA. The apparatus measures shear wave speed and calculates elasticity using the provided equation [13].

The assessments are made with the subjects in a supine position at rest and using the abdominal hollowing maneuver. Three shear modulus data points will be recorded for each muscle where the average mean is used as the relative value [38]. The system will record the shear wave velocity in meters per second (m/s), the median elasticity in kilopascals (kPa), and the measurements for depth and diameter in centimeters. Additionally, the SWE results can be presented in the form of an elasticity map, where different colors are assigned to represent varying values, creating a heatmap that visualizes the data.

#### 2.4.3. Body Composition Analysis

Dual-energy X-ray absorptiometry (DEXA) has been widely used in body composition (BC) assessments. This process involves the utilization of two previously known X-ray energies. Subsequently, the constituent photons of the X-ray beam interact with the atoms within the subject’s body, resulting in a reduction of beam intensity, a phenomenon known as beam attenuation. Finally, this attenuated beam interacts with a detector [39,40]. This process, known as attenuation, is related to the absorption, or scattering of photons depending on the thickness, density, and atomic composition of the cross structures. As so, low-density tissues attenuate the beam less than tissues with higher density, like bone tissue. Each tissue has a different attenuation and allows the DEXA the capacity to measure the coefficient of attenuation of the two power spikes issued [41]. DEXA provides BC estimations dividing the body into lean mass (LM), fat mass (FM) and bone mineral content.

For the assessment of BC with DEXA, the Biphoton Bone Densitometry Lunar—GE Healthcare, Lunar iDXA model, Software Lunar Encore for Windows version, 13.60.300 (Waltham, MA, USA) will be used (Figure 2).

The radiation used in DEXA procedures is extremely low, at 1.8/2.1 µSv for adults of both sexes [42]. This method has been used in various sports and activities such as football [43,44], rugby [45], swimming [46], and others related to physical fitness [26].

The initial step involves daily calibration in accordance with the manufacturer’s instructions. Participants wear light clothing, gym shorts and a sleeveless shirt, with no high-density artefacts on the body or clothing (metallic, plastic). The subjects are positioned in a dorsal decubitus posture within the designated evaluation area (rectangle), aligning their spine with the central longitudinal axis of the table.

Body symmetry will be confirmed and ensured. The lower limbs are fully extended, while the upper limbs were likewise extended and placed alongside the trunk, maintaining a separation from the trunk to facilitate individualized processing. The palms of the hands rest on the table in a pronated position. Total immobility is advised and confirmed for all individuals, and they are requested to refrain from talking during the assessment. All procedures, data collection, and analysis will be carried out by the same operators with more than 10 years of experience.

The outcome report includes all body composition (BC) parameters expressed in absolute values in grams or percentages, following the methodology [39]. Furthermore, dual-energy X-ray absorptiometry (DEXA) provides insights into the partial distribution of lean mass (LM), fat mass (FM), and bone mineral density (BMD) [47,48].

#### 2.4.4. Gaze Behavior Assessment

Eye tracking technology allows the study of the participants’ ocular behavior, i.e., the analysis of their eye movements and gaze behaviors during Pilates. This allows the study of smooth pursuit behaviors, saccades patterns, and fixation points, contributing to a greater understanding of the gaze behavior of Pilates participants. Upon reaching the “calibration area”, the subjects are required to focus on the calibration card, which is essential for configuring the TOBII Pro Glasses 3. This calibration procedure is repeated when the subjects switch sides (for bilateral exercises) and when they change exercises. Subsequently, the collected data will be processed using TOBII PRO LAB, following the predefined dynamic Area of Interest (AOI). Following this, the analysis will encompass time and frequency of saccades, fixations, and smooth pursuit behaviors. These AOIs are associated with the quality of movement and the success of movement execution, depending on the specific exercise being performed, with a focus on the limbs and/or hips [49]. In the analysis of gaze behavior, the collected data should be correlated with the number of saccades and the duration of each fixation within the predefined Area of Interest (AOI), tailored to each Pilates exercise. This information can also be visually represented as a heatmap, providing a spatial and temporal visualization of gaze patterns during the exercises.

#### 2.4.5. Electroencephalography (EEG)

EEG provides a set of observations (data), building a time series about the electrical activity of the brain. So, for this assessment a good level of EEG quality must be provided. Data will be collected at the frequency range of 0.16 to 43 Hz to categorize them in delta (<4 Hz), theta (4–7 Hz), alpha (7–13 Hz), and beta (14–30 Hz) waves associated with the duration and brain area of each type. These data can be presented as a heat map. To guarantee data quality, a minimum level of 75% connectivity will be set up prior to the experiment. A 32-channel Emotiv EPOC FLEX (EMOTIV PRO, 2022) will be used in EEG, which combines the flexibility and reliability of a capped electroencephalograph with wireless functionality and quick setup (20–30 min). The cortical delta, theta, alpha, and beta waves, locations, amplitude, and frequency will be collected in periods of 150 s in each exercise/side. After, amplification and digitization data are sent to a computer or mobile device for storage and data processing. Additional software will be used to read, interpret, and analyze brain waves (MatLab/MathWorks, 2021, Natick, MA, USA). These procedures allow for the identification of patterns and enrich the analysis performed [50].

#### 2.4.6. Video Motion

A Qualisys Video Motion System (Qualisys Medical AB, Sweden) equipped with 10 Oqus high-speed cameras will be used to analyze the quality of movement. This system performs real-time 3D video motion analysis, providing clear images of human movements, which allows for the analysis of trunk stabilization during exercise. The cameras are fixed on the laboratory walls, providing a complete view of the Standing Machine. The frequency used was 100 Hz. Calibration procedures were performed daily, according to the equipment manual. Forty-five reflective markers will be placed in anatomical landmarks (Figure 3) by two trained and experienced researchers [51,52].

A final anatomical check of markers will be carried out by a third researcher. The anatomical landmarks and markers were defined based on a literature review and in consultation with the operator, as shown in Table 4.

The quality of the movement for two exercises will be analyzed after this. The performance of the groups will be differentiated better in the time dimension by classifying them on a 5-point Likert scale. The scale ranges from 1 to 5, with 1 being labeled as very poor and 5 as very good performance.

#### 2.4.7. Qualitative Research

The process of combining collected data with both quantitative and qualitative methods will significantly enhance our understanding and provide insights into the phenomenon associated with the task. This approach allows us not only to explain but also to gain a deeper comprehension of the task. According to Creswell’s classification (2007) [53], the present study is categorized as a mixed study of the embedded type, due to the use of both qualitative and quantitative methods to collect data, which were carried out concurrently but with unequal weight. To proceed with this treatment, a content analysis will be carried out using NVivo software (QSR International, 2020, Burlington, MA, USA), Version number (Nvivo 14) with the definition of a priori and a posteriori categories. The interview guide will be constructed through expert submission, suggestion review, pre-testing, and application.

The interviews will be carried out by two researchers following pre-established guidelines. The interviews are expected to be recorded, typically lasting between 3 to 5 min. Subsequently, the recorded interviews will be processed. The researchers will also document the key responses from the participants in an interview grid. This comprehensive approach is intended to enhance the study’s credibility, transferability, dependability, and confirmability [54,55].

### 2.5. Operationalization/Sequence

Data will be collected after a standardized warm-up routine. After signing the informed consent forms, participants will be equipped with all technical devices needed in the “setup area”. Then, in the “calibration area”, the devices will be equipped, and the eye-tracker and EEG will be calibrated. Sequentially, an explanation of the Standing Plank exercise on a sliding platform will be presented. To ensure consistency in both content and tone, a pre-recorded instructional video will be used. Following the completion of the standing plank exercise, a second video demonstrating the side crisscross exercise will be shown. Before commencing the exercises, a 30-s setup will be recorded. Complete failure of one or both exercises will be allowed. After the data collection is completed, the subject proceeds to the “set-up area” for material disassembly procedures.

When the participants finish data collection, they will be moved to another room where the questionnaire on body image satisfaction will be completed and a semi-guided interview on the feelings and sensations of the practice will be conducted.

### 2.6. Statistical Analyses

This study seeks to contribute to the explanation and understanding of phenomena related to Pilates using a mixed quantitative and qualitative methodology. For the statistical treatment and linear analysis, IBM SPSS Statistics 28.0 software (IBM Corporation, New York, NY, USA) will be used, with a level of significance at 5% (*p* < 0.05). Descriptive statistics, including the calculation and analysis of the mean and standard deviation, will be conducted for all variables. If validation of the normality and heterogeneity assumptions of the sample are assured, then the analysis of variance ANOVA [56] will be used with multiple comparisons of means performed using the post-hoc Tukey test to verify the differences between the groups [57]. The effect size (ES) for ANOVA test is interpreted using the following criteria: no effect (ES < 0.04), minimum effect (0.04 ≤ ES < 0.25), moderate effect (0.25 ≤ ES < 0.64), and strong effect (ES ≥ 0.64) [58]. Apart from the effect size, the power (π) of the corresponding test will also be presented [59]. Pearson’s correlation analysis is defined to establish the associations between the studied variables [60].

While linear measures are useful for quantitative data analysis, taking a different perspective, non-linear data analysis is employed to characterize the collected data. This type of analysis provides insights into the organization of data within a system, offering a more nuanced understanding of the underlying patterns and structures in the dataset. The regularity, variability and complexity of the signal and the motor system in different levels of response [61,62] can lead to a larger understanding of the collected data. In fact, sample entropy can tell the amount of uncertainty attending the order of an output signal, i.e., predictability [63]. On the other hand, the Lyapunov exponent will be used to analyze the periodicity and regularity of the signal and the motor system in a time series [61]. Finally, the Hurst exponent [64,65] will be used to measure the tendency of the values of the motor system along a time scale. To proceed with the computation of the time series, the program will use UPATO [66].

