The influence of Pilates practice on neuro-muscular and cognitive function is interesting to address. Thus, research on physical activity using EEG signals, combined with nonlinear methods, will lead to new horizons in brain function research [14,15]. Recent studies point to advantages to cognitive performance in athletes compared to non-athletes [16], and it will be pertinent to obtain this knowledge in other types of activities and physical activity levels. In fact, new technologies and devices can use EEGs to study simple movements, introducing the possibility of investigating new experimental designs [17,18,19].

The gaze behavior associated with motor imagery obtained from mirror images may provide information regarding the motor control, learning speed and movement quality [20,21,22]. In activities with precise movements, such as dance, Pilates, or martial arts, the impact of the presence of a mirror and the gaze behavior of the practitioners still needs research [23]. Furthermore, the output of quality of movement, particularly if associated with other data, could be very useful for obtaining a clearer glimpse of these phenomena [24].

The objective of this study is to investigate how the Pilates method affects the learning process, motor control, and neuromuscular stabilization of the trunk, specifically in experienced and inexperienced practitioners. Secondly, it aims to identify differences in strength and muscle recruitment among the four selected muscles that we are studying. Finally, we aim to build a pattern or map of brain waves and gaze behavior, which will be created according to the practitioner’s level of experience and length of practice.

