### 2.2. Sample

We will assemble a wide-ranging and reliable sample, using a semi-randomized controlled experimental study, ensuring that our methodology is implemented. For the experimental study to produce reliable results, 39 participants will be involved, each with specific selected characteristics (Table 2). To ensure we have enough participants for our study, we used G*Power (version 3.1.9.6—software designed by the University of Kiel, Germany). Our study required a two-tailed test, with an alpha level of 0.05, power of 90%, and an effect size (d) of 1.39, which were taken into consideration during the design of our study [27,28].

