#### Eligibility Criteria

The sample for the experienced group will be selected from a local Pilates studio. Participants must have more than six months of practice, with more than 1 h of practice per week [27]. The non-expert group will be composed of subjects who must not have had any Pilates practice in the last three months. For the control group, in addition to not practicing any form of Pilates in the last three months, we also require that they not practice any form of Pilates during the study. These subjects will be allowed to maintain their physical activity routines or create new routines if body and mind activities are not included (yoga, body balance, tai-chi, among others). All groups will be composed of 13 participants between 30 and 50 years of age. The exclusion criteria are pregnancy and medical contraindications to practicing physical exercise [29].

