#### 2.4.1. Abdominal Wall Muscle Ultrasound (AWMUS)

The ultrasound study will collect data regarding RA, IO, EO, and TrA thicknesses [30]. Based on the anatomical assessment markers for each muscle, as presented in Table 3, data will be collected on the right side of the participants’ trunks both at the initial assessment and after twelve weeks of intervention. Participants lay in the supine position with their arms extended along their torso. Data will be collected in millimeters after 3 measures on the left side of the body between superficial and deeper borders of muscles to ensure the quality of measurements [31]. The mean values will be calculated to obtain a final value for each muscle in each condition. Images of the EO, IO, and TrA muscles were obtained with the transducer positioned vertically to the participant’s trunk, ten centimeters to the left of the navel, at the midpoint between the iliac crest and the last rib [32]. In the RA muscle, the transducer will be positioned horizontally right above the navel [31]. A portable ultrasound (Acuson P500) with a transducer (Siemens Healthcare GmbH, Erlangen, Germany) will be operated by one experienced researcher (>10 years). The collections will be made (a) during rest and while performing the abdominal hollowing maneuver (AHM), and (b) during a standing plank with arms back at the end of 8 repetitions.

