## 3. Results

In general, we anticipate both intra-individual and inter-individual differences that may result in statistically significant variations in the studied variables. This expectation considers the sample’s considerable diversity and variability in terms of morphological characteristics and psychomotor profiles.

Given that we have adopted both linear and non-linear analyses, which will provide a more comprehensive assessment of how the sample has evolved in terms of neuromuscular structures over both space and time, it is expected that the results may exhibit both quantitative and qualitative aspects. This will enable a mixed and more robust analysis of the applied methodology. For instance, within the context of non-linear analysis, we expect that results will show higher entropy in the expert groups when compared to non-experts. Regarding stability, the expert group is expected to exhibit higher Lyapunov exponent values compared to other groups, accompanied by lower Hurst exponent values. In the context of elastography, we anticipate that the elasticity of the transversus abdominis (TrA) muscle will be higher in experienced practitioners compared to those with less experience, both within the same group over time and when comparing across groups.

In terms of gaze behavior, results should reveal a greater number of saccades, more Areas of Interest (AOIs), and less time spent in fixation for the non-expert sample. This is because expert practitioners are assumed to have a more efficient mastery of gaze behavior.

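### For the outcomes measured twice, the stated between-groups ANOVA with Tukey uses neither visit nor baseline, so its overall result and its expert contrasts do not show learning

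*Protocol article*

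**What the plan says.** - **Objective.** Section 1 sets out to "investigate how the Pilates method affects the learning process, motor control, and neuromuscular stabilization of the trunk", in experienced and inexperienced practitioners.
- **Timing.** Section 2.4.1 takes the muscle ultrasound "both at the initial assessment and after twelve weeks of intervention". The sections on EEG, gaze and video motion state no second visit.
- **Expected result.** Section 3 expects elasticity of the transversus abdominis to be higher with more experience, "both within the same group over time and when comparing across groups". This implies that elastography is repeated as well.
- **Groups.** The Eligibility Criteria select experts on more than six months of prior practice. Non-experts start a weekly programme (section 2.3), and controls must not practise Pilates during the study. The design is called semi-randomized.
- **Group test.** Section 2.6 gives an ANOVA with "multiple comparisons of means performed using the post-hoc Tukey test to verify the differences between the groups", on the condition "If validation of the normality and heterogeneity assumptions of the sample are assured". It mentions no visit factor, group-by-visit term, change score or baseline covariate. Its other methods are descriptive statistics, Pearson correlation and signal indices (sample entropy, Lyapunov and Hurst exponents). None of these tests change between visits.

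**The concern.** Learning is a change, and the plan collects a starting value for at least one outcome. The stated test compares group means only. Because experts are chosen for what they already can do, a group difference at twelve weeks may be no more than their difference at entry. If the overall ANOVA or an expert contrast were reported as evidence about learning, the conclusion would not follow from the test.

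The comparison that does isolate training, non-expert against control, is left open to any imbalance at entry. It also forgoes precision that the baseline measurement already provides.

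Separately, the condition for using ANOVA is stated the wrong way round: ANOVA and Tukey need similar variances across groups, not different ones.

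**Working it through.** **Inputs from the protocol.** Section 2.2: "Our study required a two-tailed test, with an alpha level of 0.05, power of 90%, and an effect size (d) of 1.39", and "39 participants will be involved". Eligibility Criteria: "All groups will be composed of 13 participants between 30 and 50 years of age", so n = 13 in each of three groups.

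**Assumptions, not in the protocol.** SD 1 at both visits; an expert head start of 1.39 SD (borrowing the planning effect size); a training effect of 1.0 SD for the power comparison; pre-post correlations r from 0.5 to 0.9; and the ANOVA applied to twelve-week values, since section 2.6 does not say which visit it uses.

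**1. The plan's own sample size.** A two-sided t-test at 5% with d = 1.39 and 90% power needs 11.92, so 12 per group (power 0.902). Three groups make 36, the abstract's total. A Wilcoxon-Mann-Whitney test with relative efficiency 3/π needs 13 per group (power 0.912), and three groups make the 39 of section 2.2. Either way it is a two-group comparison with no visit term and no pre-post correlation.

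**2. Overall ANOVA at week 12.** Noncentrality λ = n Σ(μᵢ − μ̄)²; critical F(2, 36) = 3.26. Means are in the order control, non-expert, expert.
- Nobody learns, means (0, 0, 1.39): Σ = 1.39² × 2/3 = 1.288, λ = 13 × 1.288 = 16.74, rejection 0.949.
- Non-experts catch up fully, means (0, 1.39, 1.39): Σ is again 1.288, λ = 16.74, rejection 0.949.
- Nobody learns, evenly spaced means (0, 0.695, 1.39): Σ = 0.966, λ = 12.56, rejection 0.870.

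The first two situations are opposite answers to the learning question, yet they give the overall test the same distribution.

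**3. Group-by-visit test on the same data.** With two visits this is the ANOVA on change from baseline. Simulation, 20,000 runs, 13 per group:

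| Situation | r = 0.5 | r = 0.7 | r = 0.9 |
|---|---|---|---|
| Nobody learns | 0.053 | 0.047 | 0.050 |
| Non-experts gain 1.39 SD | 0.949 | 0.998 | 1.000 |

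**4. Tukey contrasts at week 12.** The critical value on the t scale is 3.457/√2 = 2.444 with 36 df, and the noncentrality is δ/√(2/13).
- True difference 0: rejection 0.020.
- True difference 1.0 SD: 0.547.
- True difference 1.39 SD: 0.858.

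If non-experts and controls start equal, their contrast rejects in about 2% of trials when nobody learns and about 86% when non-experts gain 1.39 SD. When nobody learns, each expert contrast also rejects in about 86%, from the head start alone.

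**5. Power for non-expert versus control, true effect 1.0 SD, 13 per group.** Baseline adjustment multiplies the residual variance by 1 − r².

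| Analysis of the twelve-week value | Power |
|---|---|
| Tukey across three groups | 0.55 |
| Two-group t-test, no multiplicity adjustment | 0.69 |
| Baseline covariate, r = 0.5 (factor 0.75), no multiplicity adjustment | about 0.78 to 0.79 |
| Baseline covariate, r = 0.7 (factor 0.51), no multiplicity adjustment | about 0.92 |
| Baseline covariate, r = 0.8 (factor 0.36), no multiplicity adjustment | about 0.98 |

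The covariate rows compare with 0.69, not with 0.55. Keeping multiplicity control would lower them.

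**The case against.** Four objections deserve an answer.

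- **The plan can already separate training from expertise.** A reader might infer from the 95% figure that the stated analysis cannot detect learning at all. That is too strong. The Tukey step includes non-expert versus control, and step 4 shows that it behaves properly when those groups start equal. What remains is that nothing in section 2.6 checks or adjusts for the starting values, and semi-randomized allocation does not assure equality.
- **The 95% is not a false-positive rate.** This is correct. Comparing experience levels is a stated aim, and most expectations in section 3 (entropy, Lyapunov and Hurst exponents, saccades, fixation) are expert versus non-expert contrasts. For those, finding a real 1.39 SD difference is the right answer and the ANOVA fits. The figure matters only when the result is read as learning.
- **A repeated-measures ANOVA is not excluded, and model terms may sit in a fuller document.** This is also true, and it tempers the point. But section 2.6 does commit to a test and a post-hoc procedure, and gives group differences as their purpose. That does not match the over-time expectation in section 3.
- **Visit and mirror terms cannot be imposed everywhere.** This stands. The repeat visit is stated for ultrasound and only implied for elastography. Table 1 lists mirror as an independent variable, but Tables A2 and A3 both show a mirror in place, so a mirror effect may not be estimable.

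The heterogeneity wording is probably a slip for homogeneity. It needs a one-word correction and adds little weight to the rest.

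**Conclusion.** The point holds for abdominal ultrasound, and for elastography if it is repeated as section 3 implies. For these outcomes the overall ANOVA and the expert contrasts do not distinguish learning from the experts' head start: about 95% rejection at week 12 in both opposite situations, against about 5% and 95 to 100% for a group-by-visit test. The non-expert versus control contrast is usable but unprotected against imbalance at entry, and has less power than the collected data allow (0.69 against about 0.79 to 0.98, all without multiplicity adjustment).

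These sizes rest on the assumed head start, training effect and correlations, and on 13 per group. With 12 per group the first rejection rate is 0.93. The direction does not depend on the exact values: whenever experts start ahead, a test that ignores baseline mixes that lead with any change.

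The documents do not support extending the criticism to outcomes measured once, or saying that the plan has no means of detecting training.

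**What to change.** In section 2.6:

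1. For ultrasound and elastography, name a repeated-measures or mixed model with group, visit and group-by-visit, and participant as random effect. Read learning from the interaction contrasts and expertise from the group contrast at the initial visit.
2. Compare non-expert with control on the twelve-week value adjusted for baseline. Do not use this adjustment as the main basis for contrasts with experts, who differ at entry by design.
3. Keep multiplicity control over the three group contrasts.
4. Keep the between-groups ANOVA with Tukey for outcomes measured once. State for each outcome whether it is measured once or twice.
5. Include a mirror term only where a no-mirror condition is actually recorded.
6. Change heterogeneity to homogeneity of variances, with Welch's ANOVA and Games-Howell comparisons if it fails.

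The cost is one rewritten paragraph. SPSS, already named, fits these models. Ultrasound needs no new data; elastography needs none provided the second assessment takes place as section 3 implies.
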